### Assessment of compliance with study treatment/s

All participants on intervention arms are given a treatment diary to record their daily treatment compliance. Compliance with the study treatment will be ascertained on the basis of what is recorded in the treatment diary and by recording the number of pills remaining in the packs.

### Body fat redistribution substudy

A substudy will be undertaken only for patients recruited from the North West of UK to assess whether telmisartan results in any changes in the total body adipose content and intrahepatic and intramyocellular lipid content. This will be assessed at baseline and at 24 weeks by MRI and ^1^H MRS in an on-site MRI research facility. Patients recruited will be given a separate patient information sheet and consent form containing information on the substudy and requirements for MRI/MRS. Participants will be allowed to withdraw from the substudy anytime but remain in the main study. Only patients who consent to take part in the main study and satisfy the normal MR exclusion criteria (normal MR exclusion criteria include patients using pacemakers, cochlear implants, piercings, metal in the head or elsewhere in the body, and those who suffer from claustrophobia) will be included in the substudy. MRI of the total body adipose content will be undertaken on a Siemens 1.5 T Symphony scanner (Siemens, Erlangen Germany) using well-established methods.^38^ MRI will be analysed to obtain volume estimates of total body subcutaneous, total internal, subcutaneous abdominal and intra-abdominal adipose tissue. In the same subcohort of patients, liver and skeletal muscle ^1^H MR spectra will be acquired using the Siemens body coil and Siemens CP extremity coil, respectively, using established methods.^39^ Analysis of all imaging data will be conducted centrally.

## Sample size calculation

The primary response from each patient is the difference between the baseline HOMA-IR score and their HOMA-IR score at 24 weeks. The design has been constructed under the assumption that for all patients this response is normally distributed with a common SD, σ.

The sample size calculation is based on a one-sided type I error of 5% and a power of 90%. If there is no difference between the mean response on any treatment and that on control, then a probability of 0.05 is set for the risk of erroneously ending the study with a recommendation that any treatment be tested further. For the power, we adopt a generalisation of this power requirement to multiple active treatments due to Dunnett.^40^ Effect sizes are specified as the percentage chance of a patient on active treatment achieving a greater reduction in HOMA-IR score than a patient on control as this specification does not require knowledge of the common SD, σ. The requirement is that, if a patient on the best active dose has a 65% chance of a better response than a patient on control, while patients on the other two active treatments have a 55% chance of showing a better response than a patient on control, then the best active dose should be recommended for further testing with probability 1−β=0.90. A 55% chance of achieving a better response on active dose relative to control corresponds to a reduction in mean HOMA-IR score of about a sixth of an SD (0.178σ), while the clinically relevant effect of 65% corresponds to a reduction of about half an SD (0.545σ). The critical values for recommending that a treatment is taken to further testing at the interim and final analyses (2.782 and 2.086) have been chosen to guarantee these properties using a method described by Magirr *et al*,^41^ generalising the approach of Whitehead and Jaki.^42^

The maximum sample size of this study is 336 evaluable patients, although the use of the interim analysis may change the required sample size. The study will recruit additional patients to account for an anticipated 10% dropout rate.

### Interim monitoring and analyses

An interim analysis will take place once the primary end point is available for at least 42 patients on each arm (ie, half of the planned maximum of 336 patients). The sample SD pooled across all four arms is used to construct test statistics expressing the advantage of each of the three active treatments over control. The analysis will be proceeding as follows:
If the largest test statistic exceeds 2.782, the study will be stopped and the corresponding dose will be recommended for further testing.If any active dose shows no improvement over control (ie, has a negative test statistic), that active dose will be dropped.If no active dose shows an improvement over control, the study will be stopped and no significant improvement over control will be claimed.If some improvement over control is detected for at least one dose (ie, at least one test statistic is between 0 and 2.782), the study will progress to the second stage.

At the interim analysis, doses may be dropped from the trial, or the trial may be stopped altogether. Consequently, the required sample size when the decision is reached could be smaller than the maximum stated number of 336 patients. The values 168 (if the study is stopped following interim analysis), 252 (if one active dose arm is promoted to the second stage), 294 (if two active dose arms are promoted to the second stage) and 336 (if all three active dose arms are promoted to the second stage) are possible. The reduced sample sizes refer to the numbers of patients with 24 week HOMA-IR scores which are included in the analysis. Evaluation of the patient withdrawal rate will be carried out and the sample size will be adjusted accordingly. There will be additional patients who have been recruited during the 24 weeks prior to extracting the data for interim analysis and their number will depend on the recruitment rate achieved. A decision to discontinue recruitment, in all patients or in selected subgroups, will be made on the basis of results from the interim analysis by the Independent Data and Safety Monitoring Committee (IDSMC).

## Statistical analysis

### Primary outcome analysis

Three different doses of the intervention will be evaluated against the control in stage 1 of the study and an interim analysis will take place that will allow ineffective doses to be eliminated quickly while a dose showing a positive effect can be taken forward. An ANCOVA model will be fitted for a 24 week HOMA-IR score adjusting for the stratification factor (African-American and non-African-American), and the corresponding t—values will be used to construct test statistics expressing the advantage of each of the active treatments over control. The largest of these test statistics will be compared to the interim critical value (2.782) and proceed as discussed above at the interim analysis. At the final analysis, if the largest comparative test statistic exceeds the final critical value (2.086), then this dose would be recommended for further study. Adjustments can be made to allow for any discrepancies between target and actual sample sizes while still preserving the one-sided type I error rate at 0.05.

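### The primary ANCOVA is stated for the 24-week HOMA-IR score without baseline, but the 90% power was worked out for change from baseline, so that power figure does not belong to the model as written

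*Protocol article*

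**What the plan says.** The Sample size calculation section defines the endpoint: "The primary response from each patient is the difference between the baseline HOMA-IR score and their HOMA-IR score at 24 weeks". It assumes that "this response is normally distributed with a common SD, σ", so σ is the SD of the change. Both effects are expressed in that unit. For the best dose, "the clinically relevant effect of 65% corresponds to a reduction of about half an SD (0.545σ"). For each of the other two doses, a 55% chance of a better response "corresponds to a reduction in mean HOMA-IR score of about a sixth of an SD (0.178σ"). The error rates are given as follows: "The sample size calculation is based on a one-sided type I error of 5% and a power of 90"%. The critical values for recommending a dose "at the interim and final analyses (2.782 and 2.086") are said to guarantee these properties.

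The Primary outcome analysis section then gives the model: "An ANCOVA model will be fitted for a 24 week HOMA-IR score adjusting for the stratification factor (African-American and non-African-American"). Its t-values are compared with the same two critical values. Baseline HOMA-IR is not mentioned there, and the outcome is not described as a change.

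The Interim monitoring and analyses section says: "The sample SD pooled across all four arms is used to construct test statistics". Table 1 and the Outcomes and assessments section show that fasting samples are taken at baseline, so baseline HOMA-IR will be available.

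**The concern.** A trial sized on change from baseline delivers its power if the analysis uses the change, or does better by adjusting for baseline. A model of the 24-week score with only treatment and an ethnicity factor does neither. Its error term is the spread of HOMA-IR between patients at 24 weeks, not the σ in which 0.545 and 0.178 are expressed. The same absolute treatment effect then corresponds to a different standardised effect, and the 90% no longer follows from 336 patients.

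This one statistic decides whether a dose is dropped at the interim, whether the trial stops early, and whether a dose is recommended at the end. Under the Trial interventions section, patients on a dropped dose stop the medication and leave the trial, so an unnecessarily noisy interim statistic has consequences that cannot be undone.

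**Working it through.** **Inputs from the protocol article.** One-sided familywise error 0.05 and power 0.90; effects 0.545σ, 0.178σ and 0.178σ; critical values 2.782 and 2.086 (Sample size calculation). A dose with a negative interim statistic is dropped; 42 patients per arm at the interim, with a maximum of 336, hence 336/(4 × 2) = 42 per arm per stage (Interim monitoring and analyses).

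**Assumptions, not in the document.** The correlation ρ between baseline and 24-week HOMA-IR is unknown and is varied. The SD s is taken as equal at both visits. Ethnicity is taken to explain negligible variance.

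**Step 1: reproduce the design.** The effect sizes follow from √2 × z(0.65) = 0.545 and √2 × z(0.55) = 0.178. The two-stage, four-arm design was simulated with normal responses, known variance, a shared control, dropping boundary 0, and the largest statistic recommended. With no effect, the chance of recommending any dose is 0.050. Under the design alternative, the chance of recommending the best dose is 0.906. With 41 per arm per stage it is 0.899, so 42 is the smallest number that reaches 0.90. The plan's figures are therefore right for the change score.

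**Step 2: rescale the effect for each model.**
- Change score: variance 2(1−ρ)s², equal to σ² by definition; standardised effect 0.545.
- 24-week score without baseline: variance s²; standardised effect 0.545 × √(2(1−ρ)).
- 24-week score with baseline as covariate: variance (1−ρ²)s²; standardised effect 0.545 × √(2/(1+ρ)).

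For example, at ρ = 0.7 the model without baseline has 0.545 × √0.6 = 0.422, and the model with baseline has 0.545 × √(2/1.7) = 0.591. The 0.178 effects scale in the same way.

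**Step 3: power to recommend the best dose**, 42 per arm per stage, same boundaries (simulation error affects the third decimal):

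| Assumed ρ | Model as written | Change score | With baseline as covariate |
|---|---|---|---|
| 0.3 | 0.969 | 0.906 | 0.978 |
| 0.4 | 0.947 | 0.906 | 0.971 |
| 0.5 | 0.906 | 0.906 | 0.963 |
| 0.6 | 0.835 | 0.906 | 0.953 |
| 0.7 | 0.716 | 0.906 | 0.943 |
| 0.8 | 0.533 | 0.906 | 0.932 |
| 0.9 | 0.287 | 0.906 | 0.920 |

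**Step 4: what the loss means.** To regain the design power with the model as written, the maximum sample size would be 336/(2(1−ρ)): 420 at ρ = 0.6, 560 at 0.7 and 840 at 0.8. The chance that the best dose has a negative interim statistic is Φ(−effect × √(42/2)): 0.6% at ρ = 0.5, 2.7% at 0.7 and 5.7% at 0.8.

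**Step 5: the break-even without equal variances.** The change is less variable than the 24-week score when SD_baseline² < 2ρ × SD_baseline × SD_24wk, that is, when ρ > SD_baseline/(2 × SD_24wk). Equal SDs give 0.5. If the 24-week SD were 0.8 of the baseline SD, the break-even would be 1/1.6 = 0.625.

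**The case against.** The strongest reply is that the text is being read too literally. A model with arm and a two-level factor has no continuous covariate and would usually be called ANOVA, so the word ANCOVA suggests that baseline was meant. The sample size section has already fixed the endpoint as a change, so the 24-week score may be shorthand for it. A full covariate list is also the kind of detail an article leaves to the analysis plan. This is fair as to intention, and the unseen plan may well include baseline. It does not remove the point: the article states an outcome, an adjustment and critical values for the primary model, and these do not match the response on which the trial was sized.

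Three stronger readings are tempting but not supported.
- A reader might infer that the trial is underpowered. The document gives no correlation; below about 0.5 (equal variances) the model as written has more than the stated power.
- A reader might count the pooled-SD statistic in the interim section as a further, conflicting definition. It need not conflict: t-values from a four-arm linear model also use a residual SD pooled across arms, and the analysis section refers back to the interim rules.
- A reader might treat uncorrected chance imbalance at baseline as a bias or a separate harm. Under randomisation the comparison of 24-week scores is unbiased and its type I error is kept; chance imbalance is already part of the standard error.

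**Conclusion.** The point holds as a contradiction in stated text between the sample size section and the primary analysis section. The 90% power, which reproduces as 0.906, belongs to the change score. For the model as written, power is anything from 0.969 to 0.287 over correlations of 0.3 to 0.9, crossing 0.90 at about 0.51. These figures rest on equal variances at both visits and negligible variance explained by ethnicity; the break-even moves with the ratio of the two SDs. The harm is to power and precision, at the interim as well as at the end, and not to validity. Adjusting for baseline keeps power above 0.90 at every correlation examined, so under these assumptions nothing is gained by leaving it out.

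**What to change.** Three short edits:

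1. Primary outcome analysis: state that 24-week HOMA-IR is analysed by ANCOVA with baseline HOMA-IR as a continuous covariate plus the ethnicity stratum, at both the interim and the final analysis. Using the change as outcome with the same covariates gives the same treatment test.
2. Interim monitoring and analyses: state that the test statistics are these ANCOVA t-values, with the residual SD pooled across arms.
3. Sample size calculation: note that the 90% was derived for the unadjusted change score and is conservative for the baseline-adjusted model.

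The cost is about one sentence in each section. No extra data or patients are needed, and 2.782 and 2.086 stay the same because they apply to standardised statistics. If the full protocol or analysis plan already names baseline, only the article's wording needs to be brought into line.

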### Secondary outcome analysis

Linear mixed effect models will be used to analyse secondary and mechanistic outcomes. The evaluation of beneficial and adverse biomarkers in relation to insulin resistance will be examined using the joint modelling approach^43^
^44^ accounting for informative loss to follow-up or censoring. Structural equation models^45^ will be used to assess the inter-relationship between multiple biomarkers over effect of treatment while accounting for time-varying confounders. Mechanistic outcomes such as change in body fat, liver and muscle fat distribution will be analysed using a multiple linear regression model. Differences will be considered significant at p<0.05. Differences between the groups will be estimated with 95% CIs.

## Safety reporting

The CTRC will be notified of all serious adverse reactions (SAR), serious adverse events (SAE) and suspected unexpected serious adverse reactions (SUSARs) within 24 h of the local site becoming aware of the event. The CTRC will notify the MHRA and main Research Ethics Committee (REC) of all SUSARs occurring during the study on behalf of the chief investigator according to the following timelines: fatal and life-threatening within 7 days of notification and non-life threatening within 15 days. It will also submit an annual report of all SAEs to the sponsor, MHRA and the main REC and provide the IDSMC with listings of all SAEs on an ongoing basis. The study may be prematurely discontinued on the basis of new safety information, or for other reasons given by the IDSMC and/or Trial Steering Committee (TSC), sponsor or REC concerned. All investigators will be informed of all SUSARs occurring throughout the study. The assignment of the severity/grading of adverse events will be made by the investigator responsible for the care of the participant using the Division of AIDS Table for Grading the Severity of Adult and Paediatric Adverse Events V.1.0 (2009) definitions.^46^ The CTRC will monitor SAE and ADR reporting rates across sites during the course of the trial and if any inconsistencies are noted, they will be investigated and additional training provided.

### Reporting of pregnancy

Female study participants of childbearing potential will be offered a pregnancy test as part of the trial screening process and at weeks 12 and 24. Any pregnancy which occurs during the study will be reported as an SAE to the CTRC within 24 h of the site becoming aware of its occurrence and the participant will be instructed immediately to stop taking study drugs. All pregnancies that occur during treatment need to be followed up until after the outcome. The investigator will discuss the risks of continuing with the pregnancy and the possible effect to the fetus with the participant.

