## Trial interventions

Telmisartan is an angiotensin receptor antagonist indicated for clinical use as an antihypertensive agent. It is also used to reduce cardiovascular events in patients who are at risk. However, the current trial uses telmisartan outside its licensed indications.

At the onset of the trial, telmisartan was under patent (Boehringer Ingelheim GmBH; Micardis); however, during the course of the trial, the patent expired and several manufacturers started marketing generic telmisartan, which was then also used in the trial, but the trial will continue to use Micardis SPC as the reference SPC. Telmisartan used in this trial is sourced via usual local NHS procurement arrangements.

Telmisartan tablets are available in 20, 40 or 80 mg doses and therefore fit in with the dose range to be used in the trial prior to interim analysis. In most cases, the participant is provided their required dose in one tablet. Telmisartan tablets are for once-daily oral administration and should be taken with liquid, with or without food. The CRFs will be used to record which brand has been dispensed to the participant. Telmisartan is stored as per the manufacturer's SPC.

For each randomised patient, treatment is for a maximum period of 48 weeks. The principal investigator or delegated other will issue a prescription based on the patient's randomisation status and the trial treatment can start immediately after randomisation. For the three treatment arms, treatments will be dispensed at the appropriate doses at baseline, at 12 weeks and then at 24 weeks, unless interruption or discontinuation is warranted. Wherever titration of dose is required, the treatment starts with 20 mg and is then titrated upwards over a period of 2 weeks (for a 40 mg dose) or 4 weeks (for an 80 mg dose). At 48 weeks, administration of trial treatments will be stopped and any unused medications will be returned to pharmacy for disposal via their local procedures. There is a 2 week attendance window on either side of each of the follow-up visits and a 4 day window on either side of the titration visits.

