Since the results of the interim analysis decide the design of stage II of the trial, those patients who are on a dose that is not taken forward to stage II will be asked to stop taking the medication completely. These patients will continue to be monitored for any adverse events for a period of 7 days (washout period for telmisartan) after which they will no longer be part of the trial and will return to routine care. For those who are on trial arms whose dose(s) are taken forward to stage II, they will be asked to continue on the same dose for a further 24 weeks. Since treatment is not stopped between stages I and II, some participants may receive up to a maximum of 48 weeks trial treatment before the results of the interim analysis are known. For patients recruited after the results of interim analysis are known, they will be randomised equally to the non-intervention (control) arm and the remaining telmisartan dose arm(s).

Dose modifications will be allowed in those who are randomised to a particular dose arm but do not tolerate that dose. The patient will be allowed to continue on the nearest dose tolerated. Those who show adverse effects as a result of the trial intervention or due to the HIV therapy may be withdrawn from the trial treatment. The decision to interrupt or discontinue trial therapy is at the discretion of the treating physician using their informed clinical opinion. Any changes will be documented in the CRF along with the justification for those changes. Patients who withdraw from study treatment will be asked to allow continuation of scheduled evaluations, complete an end-of-study evaluation if appropriate and be given appropriate care under medical supervision until the symptoms of any adverse event resolve or the patient's condition becomes stable. Follow-up of these patients will be continued through the trial research nurses and the lead investigator at each centre unless the participant explicitly also withdraws consent for follow-up. Data up to the time of withdrawal will be included in the analyses unless the patient explicitly states that this is not their wish.

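### No pregnancy test is scheduled after week 24, although telmisartan is dispensed then for use to week 48 with no study visit in between

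*Protocol article*

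**What the plan says.** The section Reporting of pregnancy states that women of childbearing potential "will be offered a pregnancy test as part of the trial screening process and at weeks 12 and 24". The urine pregnancy test row of Table 1 agrees: it is marked at baseline, week 12 and week 24, and is blank at week 48 and at premature withdrawal of consent. The same section requires study drug to be stopped at once when a pregnancy is known, and adds: "All pregnancies that occur during treatment need to be followed up until after the outcome".

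Under Trial interventions, "For each randomised patient, treatment is for a maximum period of 48 weeks", and "treatments will be dispensed at the appropriate doses at baseline, at 12 weeks and then at 24 weeks". Once the interim result is known, patients on a dose taken forward are covered by this: "they will be asked to continue on the same dose for a further 24 weeks". Treatment is not interrupted for the interim analysis, so "some participants may receive up to a maximum of 48 weeks trial treatment before the results of the interim analysis are known". Trial design and Table 1 place study visits at baseline and weeks 12, 24 and 48, plus titration visits at weeks 2 and 4. None falls between weeks 24 and 48.

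Baseline assessments describes telmisartan as not recommended in the first trimester and contraindicated in the second and third because of teratogenic potential. It also makes the test voluntary, since refusal does not bar entry. Reliable contraception is an entry condition for women of childbearing age (Box 1) and is named again under Ethical considerations.

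**The concern.** Up to week 24 the plan offers a test every 12 weeks, each at a visit where drug is dispensed. At week 24 the supply becomes a 24-week one, and testing ends just when the interval between visits doubles. Nothing in the article suggests that the risk of pregnancy falls after week 24.

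Two stated aims depend on a pregnancy being recognised. The first is stopping drug immediately. This is weakened mainly for conceptions in about weeks 24 to 36, which can reach the second trimester on drug. The second is following every on-treatment pregnancy to its outcome. This is weakened for a recent conception still unrecognised at week 48, because that is the last visit in Table 1. What is at stake is avoidable fetal exposure and incomplete safety follow-up in a small number of women. The statistical design is untouched.

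**Working it through.** The article gives no figure for this risk, so there is none to reproduce. The schedule comes from the article; the rates below are assumptions.

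**Test-free intervals on drug**
- Baseline to week 12: 12 − 0 = 12 weeks.
- Week 12 to week 24: 24 − 12 = 12 weeks.
- Week 24 to end of treatment: 48 − 24 = 24 weeks, with no test at the end.
- The article states: "There is a 2 week attendance window on either side of each of the follow-up visits". With the week-24 test at 22 or 26 weeks and drug stopping at 48, the last interval is 48 − 26 = 22 to 48 − 22 = 26 weeks. With both visits moved, the week 12 to 24 interval is 22 − 14 = 8 to 26 − 10 = 16 weeks.

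**What the longer interval allows**
- Assumption: the second trimester starts 12 weeks after conception.
- A conception just after the week-12 test is 24 − 12 = 12 weeks old at the week-24 test, about the start of the second trimester.
- A conception just after the week-24 test is 48 − 24 = 24 weeks old at week 48, so up to 24 − 12 = 12 weeks of second-trimester exposure can pass without a scheduled test.
- The latest conception that reaches the second trimester by week 48 is at 48 − 12 = week 36. Taking 11 or 13 weeks instead moves this to week 37 or 35.

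**Patients on a continued dose** (from the totals under Interim monitoring and analyses)
- Full arm: 336/4 = 84. Interim arm: 42.
- One dose promoted: 84 + 84 + 42 + 42 = 252. Two: 3 × 84 + 42 = 294. Three: 4 × 84 = 336. These match the article's totals.
- On continued telmisartan: 84, 168 or 252 evaluable patients.

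**Expected conceptions in weeks 24 to 48**
- Assumptions not in the article: 5% to 25% of these patients are women of childbearing potential; 1 to 10 conceptions per 100 woman-years on contraception.
- Time at risk: 24/52 = 0.4615 years.
- Formula: patients × share × rate × time.

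| | Calculation | Weeks 24 to 48 | Weeks 24 to 36 (12/24 = half) |
|---|---|---|---|
| Low | 84 × 0.05 × 0.01 × 0.4615 | 0.019 | 0.010 |
| Middle | 168 × 0.15 × 0.05 × 0.4615 | 0.582 | 0.291 |
| High | 252 × 0.25 × 0.10 × 0.4615 | 2.908 | 1.454 |

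The table treats every evaluable patient on a continued dose as taking drug to week 48. It leaves out patients on a later-dropped dose who pass week 24 before the interim result is known. If the trial stops at the interim, there is no stage II group, and only women already past week 24 on drug are affected.

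**The case against.** The strongest reply is that nothing here is misstated or contradictory. Each test falls at a visit where drug is handed out, the article nowhere sets 12 weeks as a required standard, and testing is a voluntary second line behind reliable contraception. A pregnancy that becomes known by any route must be reported and drug stopped. Study visits are fitted to routine hospital visits where possible, so week 48 need not be the site's last contact with a participant, and advice on suspected pregnancy between visits may sit in documents not shown.

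The schedule is indeed internally consistent, and these safeguards do lower the risk. But contraception, self-report and clinic contact operate equally before week 24, where the plan still offers a test every 12 weeks. They do not explain why testing stops when the supply doubles. Nor is this a detail left to the full protocol, because text and table both fix the schedule explicitly.

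Two further objections stand in part. A week-48 test cannot shorten exposure, since drug stops then; it would mainly pick up recent conceptions, and a more advanced pregnancy might surface at that visit without it. Its value is limited to the follow-up duty. The expected numbers also rest on assumed rates and span about 150-fold (2.908/0.019), and the upper end needs three promoted doses, the highest share and the highest rate together. They show that events would be few, and should not be read as a forecast.

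**Conclusion.** The point holds as a minor, low-frequency patient-safety gap. The schedule allows a nominal 24 weeks on drug without a scheduled test (22 to 26 with the window around the week-24 visit), twice the interval used earlier. On the assumed rates, about 0.6 conceptions would be expected in weeks 24 to 48 at middle values (range 0.02 to 2.9), with about 0.3 (0.01 to 1.5) early enough to reach the second trimester on drug. Recognition by the woman herself lowers these figures by an unknown share. The interval arithmetic rests on the article alone; the counts rest on the assumed share of women, conception rate and trimester boundary. The case for change is potential fetal harm set against a very small cost.

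**What to change.** 1. Mark the voluntary urine pregnancy test at week 48 in Table 1, using urine already collected at that visit, and amend Reporting of pregnancy to name weeks 12, 24 and 48. This supports follow-up of on-treatment pregnancies but does not reduce exposure.
2. At the week-24 dispensing visit, give women of childbearing potential on telmisartan a voluntary home urine test for use around week 36, with the result reported to the site. For those who use it, the longest nominal test-free stretch falls from 24 to 12 weeks (36 − 24 = 12; 48 − 36 = 12).

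An extra test at withdrawal is not needed: "Patients who withdraw from study treatment will be asked to allow continuation of scheduled evaluations", so those who only stop drug remain on the visit schedule.

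The cost is a minor amendment and test strips. With the assumed 5% to 25%, step 1 needs about 168 × 0.05 = 8 to 336 × 0.25 = 84 strips if controls are included, with no new visit or sample. Step 2 needs about 84 × 0.05 = 4 to 252 × 0.25 = 63 home tests, plus one reminder and one recorded result per woman; research nurses already send visit reminders (Patient follow-up). Its weakness is reliance on self-report, with some non-return. As 293 patients had been recruited when the article was written, the change helps only women who have not yet passed these time points.
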